#### Withdrawal of patients

A patient can withdraw from the trial at any time, at the discretion of the patient, or by the investigator if deemed medically indicated. If a participant refrains from completing the extended ECG recording protocol, he/she will remain included in the trial and in the intention-to-screen data analysis. A withdrawal of consent means that no further trial data will be collected; however, already collected data will not be erased.

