### Outcomes

#### Primary endpoint

Difference between the two arms in a combined endpoint of recurrent ischaemic stroke, intracerebral bleeding and all-cause mortality during at least 36 months of follow-up.

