#### Recruitment

Patients will be screened and included during ischaemic stroke or TIA admissions in stroke units. Participating centres report at least 200 stroke/TIA admissions yearly. With the anticipated participation of 30 sites, they need to randomise 0.6 patients weekly during the 3 years of inclusion to fulfil the recruitment target of 3262 participants.

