### Statistical methods

The main analysis of the outcome will be based on time to event (endpoint) and performed according to the intention to treat principle. The cumulative incidence of the combined endpoint and its individual components will be presented for each treatment group (standard and extended ECG).

For the primary analysis of the combined endpoint, the log-rank test will be used to test for treatment group differences. Cox proportional hazard regression will be used to estimate the hazard ratios with 95% CIs and to analyse associations with AF incidence and/or effect modification by age, comorbidity, biometrics and supraventricular activity.

The secondary analysis of each individual component of the primary endpoint will account for competing risks. We will use cause-specific models (where the rate of each individual endpoint is based on patients who have not yet experienced any of the endpoints) and subdistributional hazard models (where the rate is based on patients who have not yet experienced the endpoint under study). Other analysis, including baseline characteristics, will be presented by proportions (binary variables) and means (continuous variables) with 95% CIs in each ECG group. Corresponding group comparisons will be carried out by χ^2^ tests and t-tests. An outcome with a p value <0.05 will be considered statistically significant.

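### By elimination, major bleeding, myocardial infarction and pacemaker implantation are left to crude proportions and chi-square tests, which cannot handle censoring and have no stated time horizon

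*Protocol article*

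**What the plan says.** The Statistical methods section of the protocol article assigns methods in three steps.

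- Composite: "For the primary analysis of the combined endpoint, the log-rank test will be used to test for treatment group differences", with Cox regression for the hazard ratio.
- Components: "The secondary analysis of each individual component of the primary endpoint will account for competing risks", through cause-specific and subdistribution hazard models. Cumulative incidence is promised for the composite and its components.
- Everything else: "Other analysis, including baseline characteristics, will be presented by proportions (binary variables) and means (continuous variables", with 95% confidence intervals by arm. Then: "Corresponding group comparisons will be carried out by χ^2^ tests and t-tests".

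Major bleeding, myocardial infarction and pacemaker implantation appear under Key secondary objectives. The Secondary endpoints section lists them separately from the components of the primary endpoint.

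Three other places bear on how these outcomes accrue:

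- The Primary endpoint section counts events "during at least 36 months of follow-up". The abstract speaks of a 36-month follow-up, and the Sample size section of a fixed 3 years.
- The Recruitment section spreads enrolment over several years ("during the 3 years of inclusion").
- Withdrawal of patients: "A withdrawal of consent means that no further trial data will be collected".

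**The concern.** The three outcomes are dated register events in patients aged 70 or over. Some patients will die or withdraw consent before having the event. The plan accepts this reasoning for the components of the primary endpoint but does not extend it to these outcomes. A crude proportion has three weaknesses here.

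1. It has no place for censoring. A patient whose data stop at consent withdrawal is either counted as event-free or dropped.
2. If follow-up is open-ended, the proportion refers to no particular time point.
3. It gives no rate among patients still alive and under observation. If extended monitoring changes survival, a difference in bleeding proportions cannot be separated into longer time at risk and a higher bleeding rate.

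Major bleeding matters most, because the intervention works by putting more patients on anticoagulation. There is also an inconsistency. Code I61 receives competing-risk models as a component (Table 3), yet it is also in the code list for major bleeding (Table 4), which would be compared by chi-square.

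**Working it through.** **Which method applies.** The log-rank test is tied to the composite and the competing-risk models to its components. The three outcomes are neither, so only the catch-all sentence is left. This is an inference by elimination.

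**Inputs.** The document gives no event rate for these outcomes, so there is no figure of the plan's own to reproduce. From the document: 1631 patients per arm, follow-up of 36 months as a minimum or fixed, and 3 years of inclusion. Assumed for illustration: constant hazards, with event rate r, death rate d and withdrawal rate w per year. Follow-up of 3 to 6 years further assumes one common closing date, which the document does not state.

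**Step 1: dependence on the horizon.** With death as a competing event and no withdrawal, the expected proportion with the event by time t is

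r/(r+d) × (1 − exp(−(r+d)t)).

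With d = 0.05:

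| r per year | 36 months | 72 months |
|---|---|---|
| 0.01 | 2.7% | 5.0% |
| 0.02 | 5.4% | 9.8% |
| 0.03 | 8.0% | 14.3% |

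For r = 0.02 at 3 years: 0.02/0.07 × (1 − exp(−0.21)) = 0.2857 × 0.1894 = 5.4%. If follow-up varied between these limits, the overall proportion would be an average over an unstated mix of times.

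**Step 2: death at a fixed horizon.** The formula in step 1 is both the expected crude proportion at t and the cumulative incidence that the Aalen-Johansen estimator targets. With a fixed horizon and no withdrawal the two coincide. Both let a patient who dies at month 2 contribute no event, so death alone does not bias the proportion.

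**Step 3: withdrawal at a fixed horizon.** If withdrawn patients are counted as event-free, d becomes d + w in the formula. Take r = 0.025, d = 0.055 and t = 3. The proportion without withdrawal is 0.025/0.08 × (1 − exp(−0.24)) = 6.7%. With w = 0.01 it is 0.025/0.09 × (1 − exp(−0.27)) = 6.6%. With w = 0.04 it is 0.025/0.12 × (1 − exp(−0.36)) = 6.3%. The arm that loses more patients looks slightly safer, although the event rate is the same.

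**Step 4: size and power.** Simulation of 1631 per arm with 2000 replicates, two-sided 5%, control event rate 0.025 per year. Death is 0.055 per year and withdrawal 0.02 per year in each arm unless stated. Chi-square on crude proportions is compared with the log-rank test, which censors at death and withdrawal.

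| Scenario | Chi-square rejects | Log-rank rejects |
|---|---|---|
| No effect, 3–6 years | 4.1% | 4.3% |
| No effect, fixed 3 years | 5.0% | 4.7% |
| No effect, death 0.065 (control) v 0.055 (intervention), 3–6 years | 5.2% | 4.6% |
| No effect, withdrawal 1% (control) v 4% (intervention) per year, 3–6 years | 9.2% | 4.6% |
| No effect, withdrawal 1% v 7% per year, 3–6 years | 20.7% | 4.0% |
| Hazard ratio 1.3, 3–6 years | 66% | 67% |
| Hazard ratio 1.3, fixed 3 years | 53% | 54% |

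The Monte Carlo standard error near 5% is √(0.05 × 0.95/2000) = 0.5 percentage points. Only the two rows with unequal withdrawal show a material departure for chi-square.

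**The case against.** The strongest reply is that the article never says these three outcomes will be tested by chi-square. The sentence is a catch-all that mentions baseline characteristics, and the analysis plan, which is not shown, may set a method for each endpoint. This stands as a caution about wording. A reader might infer that the plan names chi-square for these outcomes, and it does not. But the sentence does assign a method to all remaining analyses, so the point concerns what is written and not an omission.

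A second reply concerns death. A reader might infer that crude proportions are biased because early deaths count as event-free. Step 2 shows otherwise: at a fixed horizon the recommended cumulative incidence treats them the same way. Only the cause-specific hazard ratio adds a rate among patients still at risk.

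A third reply is that follow-up may be fixed. The abstract and the Sample size section read that way, and nothing states a common closing date, so a range up to 72 months is an assumption. If 36 months is fixed for everyone, the horizon objection falls. The censoring and at-risk points remain.

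A fourth reply is that unequal withdrawal is speculative. Patients who skip patch recordings stay in the trial, outcomes come from registers, and trial contact ends after the second recording or the standard-arm ECG. Only formal withdrawal of consent stops data collection. The 20% sample-size addition also covers treatment discontinuation, so it cannot be read as a withdrawal rate. This reply stands: the simulated withdrawal rates show direction, not what this trial will see.

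**Conclusion.** The concern holds in a limited form. By elimination, three key secondary outcomes fall under a method that cannot censor at withdrawal, has no stated horizon if follow-up is open-ended, and gives no rate among patients at risk. The components of the primary endpoint are handled better, and code I61 falls under both standards.

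A reader might go further and conclude that the chi-square test is invalid here. The document does not support that. With withdrawal and follow-up balanced, the test kept its type I error and lost about one percentage point of power. Bias between arms arises only if withdrawal differs by arm. That is possible because the trial is unblinded and only one arm wears the patches, but it is not shown. All sizes rest on assumed constant rates. The gain is in interpretability, above all for major bleeding, and in protection against unequal withdrawal. The change is worth making because it costs so little.

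**What to change.** In Statistical methods, extend the approach planned for the components to major bleeding, myocardial infarction and pacemaker implantation:

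- Analyse each as time to first event, censoring at consent withdrawal or end of register follow-up.
- Report the cause-specific hazard ratio from Cox regression and the Aalen-Johansen cumulative incidence at 36 months by arm, with death as the competing event.
- Reconcile the follow-up wording in the abstract, the Primary endpoint section and the Sample size section, so that the horizon is stated once.
- Keep chi-square and t-tests for baseline variables and for outcomes without a time axis, such as adherence to the patch recording.

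The cost is one or two sentences and slightly more analysis work. The sample size does not change, and register follow-up should already supply the event dates.

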### Key secondary objectives

The key secondary objectives are to estimate the treatment effect on the primary outcome and determine if there are any differences between extended and standard ECG screening for:

Ischaemic stroke.All-cause mortalityIntracranial bleedingMajor bleeding.Myocardial infarction.Pacemaker implantation.Cost-effectiveness.

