#### Secondary endpoints

Individual components of the primary endpoint.Major bleeding, including intracranial bleeding.Myocardial infarction.Pacemaker implantation.Anticoagulation treatment.AF prevalence.Adherence to long-term ECG recording.Incidence of other prognostic arrhythmias during long-term ECG recording.

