#### Sample size

The sample size was calculated based on the primary outcome.

There were very few studies available with outcome data matching the age and morbidity of the AF SPICE trial. Very few studies on patients with an index stroke incident were available; in particular, there was a lack of data regarding patients with recent strokes and AF without OAC treatment. For this, we have made estimations and extrapolations using the very few available studies on patients with AF without OAC treatment. In particular, extrapolations have been made with regard to age since most available studies have included patients considerably younger than what is expected in AF SPICE. A list of studies used in sample size estimations is available in online supplemental appendix.

10.1136/bmjopen-2023-073470.supp1Supplementary data

For the estimations of AF detection proportions, available studies on short-term (48±24 hours) ECG recordings following stroke and corresponding studies on long-term (14 days) recordings were used. As with the outcome data, no studies with similar populations and ECG recording durations were available. Furthermore, the AF detection/incidence was estimated for the entire follow-up for both arms, reflecting the additional detection within standard care after the index event, thereby reflecting the actual risk exposure in both arms during follow-up. A list of the AF detection studies available for this estimation is reported in online supplemental appendix.

The assumptions for the sample size calculation are reported in table 2. The complete sample size calculation is provided in the appendix. For the yearly risk of the composite endpoint, we estimate 17% in patients with AF and no OAC treatment, 7.3% in patients with AF and OAC treatment and 5% risk in patients without AF. We further estimate an AF detection proportion of 6% in the control group and 19% after two ECG recordings in the intervention group, and 13% with untreated AF in the control group, resulting in a sample size of 2718 for 3 years of fixed follow-up time after inclusion. Adding 20% for participant dropouts and treatment discontinuation, a total sample size of 3262 is needed, corresponding to 1631 in each arm based on 3 years of follow-up, 80% power and a double-sided significance level of 5%. The study is powered to detect a 9% reduction in the composite endpoint in the group with extended ECG screening.

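### The p<0.05 rule is written for any outcome, and nothing separates the one confirmatory test from six key secondary comparisons

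*Protocol article*

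**What the plan says.** The protocol article has one primary endpoint, the composite of recurrent ischaemic stroke, intracerebral bleeding and all-cause mortality. Statistical methods names its test: "For the primary analysis of the combined endpoint, the log-rank test will be used to test for treatment group differences". The Sample size section rests on that outcome alone, with "80% power and a double-sided significance level of 5" per cent.

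Key secondary objectives then aims to "determine if there are any differences between extended and standard ECG screening for" a list of seven items. Six are clinical outcomes: ischaemic stroke, all-cause mortality, intracranial bleeding, major bleeding, myocardial infarction and pacemaker implantation. The seventh, cost-effectiveness, is handled by a Markov model and is not a significance test. Secondary endpoints lists "Individual components of the primary endpoint" and adds, among others, anticoagulation treatment and AF prevalence.

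Statistical methods analyses each component with two models, cause-specific and subdistribution. It uses Cox regression "to analyse associations with AF incidence and/or effect modification by age, comorbidity, biometrics and supraventricular activity". It compares the arms on other variables, including baseline characteristics, with χ² and t-tests. The paragraph ends: "An outcome with a p value <0.05 will be considered statistically significant".

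**The concern.** The closing sentence applies to an outcome of any rank. It comes directly after the text on the component analyses and the other group comparisons, so it is hard to read as meant for the primary alone. Read literally, it allows a secondary outcome to be called significant at a nominal 5% even if the composite shows no difference. The key secondary objectives are worded as questions to be decided, which invites that use.

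Two details add to this. Each component gets two models that estimate different quantities and may disagree, and the article does not say which one carries the test. The arms are also to be compared by test on baseline characteristics. Under proper randomisation every baseline null hypothesis is true, so a small p-value there is a chance finding.

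What is at stake is how a component or bleeding result would be presented if the primary is neutral. The abstract expects positive results to pass rapidly into clinical practice, so the status of each claim should be settled before the data are seen.

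**Working it through.** **Inputs from the article**
- Threshold per outcome: p<0.05, unadjusted (Statistical methods).
- Primary tests: one, two-sided 5% (Statistical methods; Sample size).
- Key secondary between-arm clinical comparisons: 7 listed − 1 (cost-effectiveness, a model) = 6 (Key secondary objectives).

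**Input not in the article**
- Correlation between the six test statistics. This is an assumption, taken as a common value from 0 to 0.8. Some positive correlation is expected because Secondary endpoints counts intracranial bleeding within major bleeding.

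**Step 1: the primary test.** With one test, 1 − 0.95 = 0.05. This agrees with the two-sided 5% in the Sample size section. The secondary analyses do not change it. The article states no familywise figure for the secondaries, so there is none to reproduce.

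**Step 2: six independent tests, all nulls true.** 1 − 0.95^6 = 1 − 0.7351 = 0.2649, or 26.5%.

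**Step 3: six correlated tests, all nulls true.** With common correlation ρ and cut-off c = 1.96, condition on a shared standard normal factor u:

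P(at least one) = 1 − ∫ φ(u) · [Φ((c − √ρ·u)/√(1−ρ)) − Φ((−c − √ρ·u)/√(1−ρ))]^6 du

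| Assumed common correlation | At least one p<0.05 |
|---|---|
| 0 | 26.5% |
| 0.3 | 24.1% |
| 0.5 | 20.7% |
| 0.7 | 16.4% |
| 0.8 | 13.9% |

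**Step 4: sensitivity to the count.** If the two bleeding outcomes are set aside as safety estimates, four tests remain: 1 − 0.95^4 = 18.5% when independent.

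**Step 5: what control would give.** Bonferroni over six tests uses 0.05/6 = 0.0083, and 1 − (1 − 0.0083)^6 = 4.9% when independent, at most 5% under any correlation. A fixed sequence opened only by a significant primary also holds the rate at or below 5%. An exploratory label removes the significance claim altogether.

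**Not counted.** The second model per component, anticoagulation treatment, AF prevalence and the effect-modification analyses are left out. The article does not fix how many tests these would be.

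**The case against.** The strongest reply is that a protocol article may leave multiplicity to the SAP, which is not shown, and that the sentence is a conventional statement of a nominal threshold. The endpoints are clearly tiered: one primary, one named test, a sample size built on it, then key and other secondaries. A reader can tell which result is confirmatory, and nothing here stops an SAP from setting an order.

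Much of this stands. Silence on multiplicity would be no finding, and the primary type I error is intact. What remains is that the article is not silent. It states a rule for any outcome, while the tiers carry no testing rule. The word exploratory is attached to outcomes only under data collection, where no outcome is assigned to it. An SAP with a hierarchy would have to override the published sentence.

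Some stronger readings are tempting and are not supported:
- A reader might infer that the plan promises 5% overall and delivers 20–26%. The 5% in the Sample size section belongs to the primary test only. The 20–26% range also needs all six nulls to be true and a correlation no higher than about 0.5.
- A reader might add that anticoagulation could lower ischaemic stroke and raise bleeding, so that a neutral composite with one significant component is likely to be a false claim. If those effects are real, the component results are true positives. The figures above assume no effect on any of the six, so they do not measure that scenario.
- A reader might extend the count to subgroup interactions. The article names factors to examine but not a number of interaction tests, so a larger figure would rest on invented counts.
- A reader might say the p<0.05 rule itself covers the baseline tests. It speaks of outcomes, which baseline variables are not. The objection to those tests is separate: they answer no useful question.
- Reporting both competing-risk models is sound in itself. The gap is only that no lead model is named.

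**Conclusion.** The point holds as a fault in a stated rule, and a modest one. As written, the sentence in Statistical methods lets any of six key secondary comparisons be called significant at a nominal 5%, whatever the primary shows. If none of the six outcomes truly differed, at least one would reach p<0.05 in about 26% of trials with independent tests, 21% with a common correlation of 0.5, and 14% with 0.8. The size depends on that global null and on a correlation that the article does not give. The primary analysis, its error rate and its power are unaffected. If the SAP already sets a hierarchy or an exploratory label, the remedy is simply to bring the published sentence into line with it.

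**What to change.** Replace the closing sentence of Statistical methods with a rule to this effect: the only confirmatory criterion is p<0.05, two-sided, on the log-rank test of the primary composite; secondary, component and effect-modification analyses are exploratory and are reported as estimates with 95% CIs. Allow one exception: the SAP may pre-specify a hierarchy of key secondary outcomes, conditional on a significant primary, provided it is fixed before register data are extracted. Whether to have a hierarchy, and in what order, is the sponsor's choice.

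In the same paragraph:
- report bleeding outcomes as safety estimates with 95% CIs in all cases;
- name one lead model, cause-specific or subdistribution, for each component, with the other as supportive;
- drop the significance tests of baseline characteristics and keep the descriptive summaries.

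The cost is one paragraph in the protocol or SAP, with no extra patients or data and no loss of power for the primary test. The downside is that a secondary outcome with nominal p<0.05 can no longer be claimed as significant on its own.

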### Data monitoring committee

An independent Data Safety and Monitoring Board (DSMB) will be appointed at the start of the main trial, that is, after the pilot phase. The DSMB will have a consulting role on the steering committee. The DSMB will monitor and annually provide statements on:

Cumulative inclusion rate, balance in baseline characteristics, duration and yield of ECG recordings during the inclusion phase.Event rate in the standard and intervention groups annually.

### Harms

All diagnostic tools used in the trial are approved by regulatory bodies. Any adverse events noted in connection with investigations or treatment should be reported to authorities according to practice.

